### Ethics

This protocol was submitted to the National Institute of Health Doutor Ricardo Jorge Ethics Committee (INSA-EC) in 2024 July 19^th^ and approved on July 30^th^.

## Discussion

This article outlines the conceptual framework and methodological approach to estimate high-dose quadrivalent IVE using EHR in the community and LTCF. We intend to estimate the risk of hospitalisation reduction by comparing two vaccination strategies (High-dose quadrivalent influenza vaccine and standard-dose influenza vaccine – rIVE), and comparing vaccinated with unvaccinated individuals (absolute IVE). To date, retrospective cohort studies regarding high-dose quadrivalent IVE in reducing influenza-related hospitalisation of individuals aged 65 or older have been conducted using specific populations, such as United States veterans or health insurance beneficiaries [10–13]. To the best of our knowledge, studies on the effect of high-dose influenza vaccines in LTCF remain limited to immunogenicity studies.

Given the population under study, LTCF and community-dwelling individuals (≥85 years), the potential low vaccine coverage in the eligible population, and the absence of specific studies designed to collect data in LTCF settings, we decided to use routinely collected data in electronic health registries to estimate the high-dose quadrivalent IVE. This approach has already been used successfully to estimate COVID-19 VE [14], and allows VE monitoring with good precision and high representativeness [15–18].

Despite its strengths, this study also has some limitations. We plan to use EHR, which does not aim to collect data for research purposes. Thus, this could lead to misclassification bias regarding vaccine status, outcomes, and confounding variables. For this reason, we might be unable to control for residual confounding since many relevant variables are not monitored or available in registries, and one should be aware that estimates can vary in the presence of confounding. Additionally, unvaccinated individuals will be the reference group when estimating absolute IVE. However, these individuals might differ from the vaccinated individuals due to their clinical profile or possible misclassification bias. Thus, we will use propensity score matching to account for this, assigning a probability of being vaccinated to each individual based on covariates. Considering that we will use EHRs, we might also be unable to correctly identify all individuals living in LTCF, as the report might vary geographically and temporally. Additionally, identifying these individuals might be associated with a differential bias, assuming that vaccinated individuals might be more likely to be reported as living in LTCF than unvaccinated. This situation is less likely to be problematic when estimating relative and absolute IVE in the community.

Another limitation is the potential outcome misclassification. In VE studies, it is extremely important to have sensible outcome definitions as the vaccines are designed to protect against influenza and related complications and studies use laboratory-confirmed outcomes. Using specific influenza ICD codes to identify severe influenza could underestimate severe influenza as the diagnosis is highly dependent on the testing strategy and, thus, on the codification attributed at discharge. On the other hand, including a broader range of ICD codes in the outcome definition could also underestimate IVE by including non-influenza-related outcomes. To balance this, we intend to use ICD codes that have been used for a long time in influenza surveillance and are highly sensitive. Finally, we intend to use discharge codes, as they are the final primary diagnosis of the hospitalisation. However, there are delays in hospital discharge and the codification of the hospitalisation event. In order to minimise this, the retrospective study will only use end-of-season data.

In conclusion, the study aims to produce estimates of high-dose IVE in the population eligible for the high-dose vaccine and contribute to the overall knowledge of the potential added protection provided by this vaccine. Given the vaccination strategy implemented in this population and the national effort in acquiring and implementing vaccination strategies, evaluating the effect of such public health intervention is crucial. The results will also inform decision-makers in future IVE. Additional future studies should include, not only relative indicators, but also quantitative measures of the vaccination strategy’s impact on the population [19].

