This high-dose quadrivalent vaccine presented higher efficacy in a randomized clinical trial versus a standard-dose influenza vaccine for preventing laboratory-confirmed influenza illness in adults aged 65 or more [3]. Systematic reviews and meta-analyses, which included randomized and observational studies, assessed the effectiveness of high-dose inactivated influenza vaccines versus standard-dose influenza vaccines against influenza-related outcomes in 65 or more years old individuals [6,7]. The results support the evidence on the effectiveness of high-dose inactivated influenza vaccines compared to standard-dose influenza vaccines in preventing severe influenza outcomes in 65 or more years old individuals, with additional support from observational data [7]. Regarding severity-related outcomes, the high-dose quadrivalent influenza vaccine was more effective than the standard-dose influenza vaccine in preventing influenza-related hospitalisations, with a relative influenza vaccine effectiveness (rIVE) of 11.2% (7.4%-14.8%) for all seasons. Despite the important evidence of the effectiveness of the influenza vaccine (IVE) of the high-dose inactivated influenza vaccines for individuals aged 65 or older, only three studies in nursing homes were included [6]. Review studies indicated a need for further real-world population-based studies of high-dose influenza vaccines. Hence, it remains necessary to assess the clinical effectiveness of this vaccine in older adults living in LTCF [7–9].

In Portugal,in 2022–2023 season [10], the high-dose quadrivalent influenza vaccine began to be available exclusively and free of charge for individuals aged 65 or more living in long-term care facilities (LTCF). In the 2023–2024 season, access was expanded to community-dwelling individuals aged 65 or more, who could receive the vaccine in community pharmacies with co-payment upon medical prescription [11]. Since the 2024–2025 season the high-dose influenza vaccine is available for individuals aged 60 or more and offered free of charge to all individuals aged 85 or more, regardless of residence setting, in addition to continued free access for residents in LTCFs and similar institutions [12].

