**Fig 1 pone.0314177.g001:**
[figure not shown]
Diagram of the two cohorts designed in this study. A – cohort of vaccinated individuals to measure relative influenza vaccine effectiveness, B – cohort of individuals eligible for the high-dose influenza vaccine to measure absolute influenza vaccine effectiveness. For the two cohorts, we will consider two subgroups: community-dwelling individuals aged ≥85 years and individuals living in LTCF and each cohort will begin every influenza season.

We will use a fixed cohort approach, defining the eligible population by their age at the start of the vaccination campaign(s) and living status. Table 1 describes the connection between the cohorts and the objectives.

**Table 1 pone.0314177.t001:** Summary of the study design with the different cohorts, objectives and exposed and unexposed groups.

Cohort	Subgroup	Objective	Exposed	Reference group
Vaccinated individuals (Fig 1, panel A)	Individuals living in LTCF	Estimate relative IVE of the high-dose quadrivalent influenza vaccine	Vaccinated with high-dose quadrivalent influenza vaccine	Vaccinated with standard influenza vaccine
	Individuals living in the community (≥85 years)			
Individuals eligible for influenza vaccination (Fig 1, panel B)	Individuals living in LTCF	Estimate absolute IVE of the high-dose quadrivalent influenza vaccine	Vaccinated with high-dose quadrivalent influenza vaccine	Unvaccinated individuals eligible for the high-dose quadrivalent influenza vaccine
	Individuals living in the community (≥85 years)			

IVE – influenza vaccine effectiveness; LTCF – long-term care facilities

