### Inclusion and exclusion criteria

The study population includes all registered individuals without contraindications for influenza vaccination residents in mainland Portugal. Only vaccinated individuals with the high-dose quadrivalent or standard influenza vaccine living in LTCF or community-dwelling individuals aged 85 or older will be included to estimate rIVE. Whereas, to estimate absolute IVE, only eligible individuals for the high-dose influenza vaccine living in LTCF or community-dwelling individuals aged 85 or older will be included.

We will exclude individuals with inconsistent or missing data on vaccination (e.g., any vaccination date unknown and any vaccine brand unknown), individuals who received any vaccine brand not approved by the European Medicines Agency (EMA), and individuals vaccinated before the study started.

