### Study setting and period

To estimate rIVE, the study population will include individuals vaccinated with the high-dose or standard influenza vaccine in mainland Portugal between the 2022/2023 and 2024/2025 seasons. When applicable, we will analyse each season (2022/2023, 2023/2024, 2024/2025) individually, starting after the implementation of each influenza vaccination campaign and ending nine months thereafter.

To estimate absolute IVE, the study population will include individuals for whom the high-dose influenza vaccine has been recommended in mainland Portugal for the 2024/2025 season. The study period will start after the implementation of the influenza vaccination campaign period and end nine months thereafter.

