### Stratification variables

If possible, and when applicable, rIVE will be estimated for each seasonal campaign.

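### Community (85 or more) relative IVE is not restricted to seasons with community access to high dose, so in 2022/23 its exposed arm would be essentially unrecorded LTCF residents or registry errors

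*Protocol article*

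**What the plan says.** **Access to high dose (Background).** In 2022/23 the vaccine "began to be available exclusively and free of charge for individuals aged 65 or more living in long-term care facilities (LTCF"). In 2023/24 "access was expanded to community-dwelling individuals aged 65 or more, who could receive the vaccine in community pharmacies with co-payment upon medical prescription". From 2024/25 it was "offered free of charge to all individuals aged 85 or more, regardless of residence setting".

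**Who enters the relative analysis.** For relative IVE, the section on inclusion and exclusion criteria reads: "Only vaccinated individuals with the high-dose quadrivalent or standard influenza vaccine living in LTCF or community-dwelling individuals aged 85 or older will be included to". No season is attached to the community subgroup there or in Table 1, and the Fig 1 caption has "individuals living in LTCF and each cohort will begin every influenza season".

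**Which seasons.** Study setting and period defines the relative-IVE population over 2022/23 to 2024/25 and adds: "When applicable, we will analyse each season (2022/2023, 2023/2024, 2024/2025) individually". Stratification variables states, with the qualifiers that it must be possible and applicable, that "rIVE will be estimated for each seasonal campaign". Absolute IVE, by contrast, is confined to 2024/25.

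**Residence recording (Discussion, limitations).** "we might also be unable to correctly identify all individuals living in LTCF, as the report might vary geographically and temporally". The paragraph adds that vaccinated people may be more likely than unvaccinated people to be recorded as LTCF residents. It then judges the situation less likely to cause trouble for relative and absolute IVE in the community. It gives no figure and does not distinguish seasons.

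**The concern.** The Discussion treats missed residence as a matter of vaccinated against unvaccinated people. In the relative analysis everyone is vaccinated, and what counts is how missed residents divide between the high-dose and standard-dose arms. Access to high dose depended on residence and changed each season, so the make-up of the community high-dose arm changes with it.

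The extreme case is 2022/23. A correctly classified community-dweller had no programme access to high dose. The community high-dose arm is then either empty or filled by people whose residence was not recorded, plus registry errors. A hazard ratio from that arm compares LTCF residents on high dose with community-dwellers on standard dose, under the label of community relative IVE.

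The Background describes LTCF residents as frail and more susceptible to severe outcomes. If that excess risk survives adjustment, early-season community relative IVE is biased downward and an apparent improvement over seasons can follow. The Abstract says that the results will inform the Health Ministry on the future vaccine programme.

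**Working it through.** The article gives no misclassification rate, high-dose uptake, LTCF share or event count, so there is no figure of its own to reproduce. The check has two parts.

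**1. What follows from the text alone.** Let *p* be the share of the community high-dose arm that is missed LTCF residents:

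*p* = L·m·hL / (L·m·hL + hC)

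- L: ratio of LTCF residents to community-dwellers at 85 or more
- m: fraction of residents missed by the flag
- hL, hC: high-dose uptake in LTCF and in the community

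Exclusive access in 2022/23 means hC = 0. Then *p* = 1 for any L, m and hL above zero. This needs no assumption about flag sensitivity or about which vaccine most missed residents received. If 0.1-0.5% of community-dwellers carried off-programme or miscoded high-dose records, *p* would be 20-99% (median 81%) over L 0.05-0.20, m 5-40% and hL 50-90%. Those that are not missed residents are then the errors themselves.

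Over the same ranges for L, m and hL:

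| Season | Assumed hC | *p*, range (median) |
|---|---|---|
| 2023/24 | 0.5-10% | 1-94% (26%) |
| 2024/25 | 20-70% | 0.2-26% (2.3%) |

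**2. Illustration of the effect on relative IVE.** Let *q* = L·m·sL / (L·m·sL + sC) be the missed share of the standard-dose arm, with sL and sC the standard-dose uptakes. Let R be the hazard ratio of missed residents against community-dwellers after adjustment. Then

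apparent HR = 0.888 × (1 − p + pR) / (1 − q + qR)

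The 0.888 is 1 − 0.112, from the literature value of 11.2% quoted in the Background, held constant over seasons. All else is assumed: L = 0.10, m = 0.20, hL = 0.8, sL = 0.1; (hC, sC) = (0, 0.70), (0.03, 0.67), (0.60, 0.10).

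- L·m·hL = 0.016, so p = 0.016/0.016 = 1; 0.016/0.046 = 0.348; 0.016/0.616 = 0.026.
- L·m·sL = 0.002, so q = 0.002/0.702 = 0.003; 0.002/0.672 = 0.003; 0.002/0.102 = 0.020.
- At R = 1.5 in 2022/23: 0.888 × 1.5 / 1.0014 = 1.330, that is -33.0%.

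| R | 2022/23 | 2023/24 | 2024/25 |
|---|---|---|---|
| 0.8 | 28.9% | 17.3% | 11.3% |
| 1.0 | 11.2% | 11.2% | 11.2% |
| 1.25 | -10.9% | 3.6% | 11.1% |
| 1.5 | -33.0% | -4.1% | 10.9% |
| 2 | -77.1% | -19.3% | 10.6% |

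Over a wider grid, the spurious change from 2022/23 to 2024/25 is +7 to +11 points at R = 1.1, +37 to +52 at R = 1.5, and -15 to -23 at R = 0.8.

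**Who is missed also matters.** If missed residents mostly had standard dose (hL = 0.2, sL = 0.7), R = 1.5 gives -32%, +7% and +16%. The 2024/25 estimate is then biased upward.

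**Pooling.** Add the three seasons with equal size and baseline hazard, ignoring season in the model. Then p = 0.048/(0.048 + 0.63) = 0.071 and q = 0.006/(0.006 + 1.47) = 0.004. Apparent relative IVE is 8.2% at R = 1.5 and 5.3% at R = 2. Without 2022/23, p = 0.032/0.662 = 0.048 and q = 0.004/0.774 = 0.005, giving 9.3% and 7.4%. Dropping 2022/23 removes part of the bias, not all.

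**The case against.** **The plan may never intend a 2022/23 community estimate.** The season-specific analyses are qualified twice, the Abstract ties the community extension to 2024/25, and Propensity score matching lists positivity as a requirement, which a 2022/23 community high-dose arm fails. This has weight: the article does not commit to that estimate, nor does it set out a pooled model. But the qualifiers govern only the season-by-season analysis. The population definition covers all three seasons without restriction, whereas absolute IVE is explicitly limited to 2024/25.

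**A reader might infer that community relative IVE must rise over seasons, from an arm made up wholly of missed residents to one with a few percent.** The documents do not support that. A rise needs R above 1 after adjustment for age, comorbidity and the other planned covariates, and a constant true relative IVE. The Background makes R above 1 plausible but also mentions different exposure in the community through more contacts. A small 2024/25 share rests on assumed uptake. That missed residents are mainly high-dose recipients is inferred from access policy, and Table 1's LTCF comparison presupposes some residents on standard dose.

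**The limitation is already disclosed, and in 2024/25 the comparative reassurance may be fair.** Both stand. With mainly high-dose missed residents the illustration moves 2024/25 by about half a point at R = 2. The disclosure does not reach 2022/23, where the reassurance is wrong.

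**Adjustment or matching might deal with it.** It cannot be relied on to do so: true residence is the unmeasured variable, and in 2022/23 true community-dwellers had no programme access to high dose.

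**Conclusion.** The point holds in this form. Community relative IVE is not estimable in 2022/23, on the article's own statement of exclusive access and whatever the accuracy of the flag. Nothing in the population definition keeps those records out of a pooled estimate. The Discussion's reassurance fails for that season and is doubtful for 2023/24, where access was by prescription with co-payment; for 2024/25 contamination is probably small.

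Size and direction beyond 2022/23 are not established. They depend on the LTCF share, flag sensitivity, high-dose uptake in each setting and the adjusted hazard of missed residents, none of which the article gives. If that hazard ratio exceeds 1, early community relative IVE is biased downward and a spurious upward trend can appear; at 1 there is none, and below 1 it reverses. Nor is it shown that a pooled estimate would mainly reflect the flag: in the illustration it falls from 11.2% to 8.2% or 5.3%.

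**What to change.** 1. In Study setting and period and in Stratification variables, restrict community relative IVE, season-specific and pooled, to 2023/24 and 2024/25.
2. Tabulate by health region the share of 2022/23 high-dose recipients aged 65 or more, and 85 or more, who are flagged as LTCF residents. This approximates flag sensitivity among vaccinated residents. It is valid only if the flag is not itself derived from high-dose receipt, and it counts off-programme or miscoded records as missed residents.
3. Use that figure as one input to a sensitivity analysis of community relative IVE in 2023/24 and 2024/25. Vary it over a range, because the article itself says recording changes over time and one season's value cannot simply be carried forward.
4. Qualify the Discussion sentence so that it no longer covers community relative IVE in 2022/23.

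The cost is wording and a tabulation of data that will be linked anyway. The downside is that there is no 2022/23 community estimate, and that the check speaks only for vaccinated residents in one season.
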